### Rates of imaging

Rates of imaging required, including x-rays, CT or MRI, will be compared between trial arms. In particular, the frequency of x-ray imaging (i.e. the number of individual x-rays performed) in the patients diagnosed with ‘no’ or ‘buckle’ fracture in each trial arm will be determined.

### ED length of stay

The length of stay (LOS) in the ED for each patient will be determined from the electronic clinical record. This will be defined from the time the patient was triaged to the time of discharge (home or admission to the ward). Treatment time will also be noted, defined as the time from clinical review of the patient until time of discharge from ED.

### Diagnostic accuracy

The diagnostic accuracy of POCUS and x-ray imaging will be determined against the gold standard final diagnosis, as determined by the consensus from an expert panel based on the clinical course, investigations and final management. The expert panel will meet regularly throughout the course of the study. A case is defined as ‘true positive’ when POCUS diagnoses ‘any’ fracture type (i.e. ‘buckle’ and ‘other’ fractures combined). A “true negative” is defined when ‘no’ fracture is identified on POCUS, matching the expert panel final diagnosis. A “false positive” is defined when ‘any’ fracture is identified on POCUS but the final diagnosis is ‘no’ fracture. A “false negative” occurs when ‘no’ fracture is found on POCUS but the expert panel identifies ‘any’ fracture. Given that buckle fractures can be managed more in keeping as a soft tissue injury, we will secondarily compare the ‘other’ fractures against ‘buckle’ and ‘no’ fracture groups combined. The same definitions will apply for the x-ray arm of the trial, for which the clinician interpretation of the x-ray at time of discharge will be compared to the gold standard diagnosis. The diagnostic utility of POCUS secondary signs and clinical findings will be evaluated.

### Ethical considerations

Once recruited, patients will be de-identified and assigned a study number linked to their hospital record number. Initial data collected by the clinician will be recorded on hardcopy case report forms, which will then be stored in a locked cabinet along with consent forms to be later entered into the electronic database. Participants will be emailed the questionnaires with direct data entry electronically captured in the password protected REDCap® database.

### Statistical methods

Summary statistics will be presented as either mean (SD) or median (25th–75th percentile) for continuous data, depending on their distribution, and as frequency (percentage) for categorical data. For the primary outcome, physical function assessed by the PROMIS tool at 4 weeks, we assess non-inferiority of POCUS within a 5-point margin. The between-group difference at 28 days will be assessed using linear regression modelling with treatment group (POCUS/x-ray) included as a main effect. Non-inferiority will be established if the 95% confidence interval for the difference between-groups is completely above the non-inferiority margin. Primary analyses will include all randomised patients. A secondary analysis of the subgroup of patients confirmed to have buckle fractures by the expert panel will be undertaken. Analysis will be on an intention-to-treat basis, with a secondary per-protocol analysis undertaken.

Secondary outcomes such as costs, satisfaction, pain, complications, rates of imaging, length of stay and diagnostic accuracy for the two study groups will be compared. Linear regression models will be used to compare continuous outcomes, logistic regression models will be used to compare dichotomous outcomes, and Poisson regression models will be used to compare count outcomes. Subgroup analyses will be performed for each category of ‘no’ fracture, ‘buckle’ fracture and ‘other’ fracture, and also for age category (5–9 and 10–15 years), given that healing rates may differ in these age groups. Missing data will not be imputed.

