#### Sample size

Sample size calculations were based on a non-inferiority hypothesis comparing POCUS with x-ray (routine care) for the primary outcome of upper limb function assessed using the PROMIS score at 4 weeks. Previous studies suggest the true between-group difference was assumed to be zero with the non-inferiority margin defined as an absolute difference of 5 points and the standard deviation of PROMIS assumed to be 11.5 points [21–23]. To achieve 90% power with a one-sided α of 0.025, we require primary outcome data for 224 children (112 per arm).

A key secondary endpoint is to assess the non-inferiority of POCUS compared with x-ray as the initial imaging strategy for children who are later confirmed by the expert panel to have buckle fractures. Previous studies suggest that the standard deviation of PROMIS for children with buckle fractures is approximately 7.5 points [21–23]. Assuming the true between-group difference is 0 and defining the non-inferiority margin as 5 points, then with 90% power and one-sided *α* = 0.025, we require primary outcome data on 96 children with buckle fractures (48 per arm). We assume 35–45% of participants will be diagnosed with buckle fractures by the expert panel.

Recruitment will continue until primary outcome data has been collected on both at least 112 children per arm and at least 48 buckle fractures per arm. Allowing for approximately 25% attrition and variation in buckle fracture prevalence, we expect to recruit up to 300 patients to achieve the required sample size.

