#### Randomisation

Randomisation to either POCUS or x-ray as the initial diagnostic modality will be computer-generated via a web-based central randomisation service (Griffith University Clinical Trials Randomisation Service). Randomisation will occur in a 1:1 ratio within blocks of size 6–8 (size randomly selected), stratified by site and age (5–9 years and 10–15 years). Secure, password-protected web-based randomisation will occur once; the participants’ eligibility has been confirmed by the clinician and baseline data collected. Randomisation to intervention will be generated by any credentialed clinician available to perform POCUS.

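### The stated primary model names treatment group alone although randomisation is stratified by site and age; if either predicts PROMIS, the non-inferiority interval is somewhat too wide

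*Protocol article*

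**What the plan says.** Under Randomisation, allocation is 1:1 in permuted blocks of 6 to 8, "stratified by site and age (5–9 years and 10–15 years". Under Statistical methods, the primary analysis is set out in one sentence: the arms are compared at 28 days by "linear regression modelling with treatment group (POCUS/x-ray) included as a main effect". No other term is named for that model there, and nowhere else does the article say that the primary comparison adjusts for site, age or a baseline score. Age group returns in the same section only as a subgroup factor, "given that healing rates may differ in these age groups".

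Non-inferiority is decided by whether the whole 95% confidence interval lies above the margin. Under Sample size, the margin is 5 points, the outcome has its "standard deviation of PROMIS assumed to be 11.5 points", and "the true between-group difference was assumed to be zero". With a one-sided α of 0.025 and 90% power, this leads to 112 children per arm with primary outcome data.

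**The concern.** Stratified blocked allocation holds the arms close to balance on site and age. Whatever those factors contribute to PROMIS then largely cancels from the treatment difference. A regression on treatment alone does not know this. It counts the between-stratum variation as residual noise, so its standard error overstates the real sampling error of the difference. The trial is decided by one confidence limit against one margin, so an interval wider than necessary makes non-inferiority harder to show, and the actual one-sided error falls below the stated 0.025.

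The article gives reasons to think the strata may be prognostic. It says that healing may vary with age group. It has PROMIS completed by proxy below 8 years and by the child from 8. It also plans a mix of tertiary and non-tertiary hospitals, and of paediatric and mixed emergency departments.

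**Working it through.** **Inputs from the article (Sample size, Randomisation, Statistical methods):** margin 5; SD 11.5; true difference 0; one-sided α 0.025; power 90%; 112 per arm analysed; about 25% attrition; up to 300 recruited; strata of site × two age groups.

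**Input not in the article:** R², the share of PROMIS variance explained by site and age. It is an assumption, shown as a range. The number of sites is not given either.

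**Step 1. Reproduce the planned size.** n per arm = 2(1.960 + 1.282)² × 11.5² / 5² = 111.2, rounded up to 112. This matches the article, so the planned size rests on the full, unadjusted SD.

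**Step 2. Unadjusted precision.** SE = 11.5 × √(2/112) = 1.537. Half-width = 1.96 × 1.537 = 3.01 points. Power = Φ(5/1.537 − 1.96) = 90.2%.

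**Step 3. Effect of the strata.** With adjustment, the residual SD is 11.5 × √(1 − R²).
- Adjusted half-width = 3.012 × √(1 − R²).
- Adjusted power = Φ(5 / (1.537√(1 − R²)) − 1.96).
- Actual one-sided error of the unadjusted interval, with arms perfectly balanced within strata = 1 − Φ(1.96 / √(1 − R²)).
- Actual power of the unadjusted interval under the same balance = Φ((5 − 3.012) / (1.537√(1 − R²))).

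| Assumed R² | Half-width unadjusted | Half-width adjusted | Unadjusted wider by | One-sided error, unadjusted | Power unadjusted | Power adjusted |
|---|---|---|---|---|---|---|
| 0 | 3.01 | 3.01 | 0% | 0.025 | 90.2% | 90.2% |
| 2% | 3.01 | 2.98 | 1.0% | 0.024 | 90.4% | 90.8% |
| 5% | 3.01 | 2.94 | 2.6% | 0.022 | 90.8% | 91.6% |
| 10% | 3.01 | 2.86 | 5.4% | 0.019 | 91.4% | 92.9% |

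**Step 4. What these R² values mean.** For two age groups of equal size whose means differ by d points, R² = 0.25d² / 11.5². A 3-point gap gives 2.25/132.25 = 1.7%, and an interval about 1% wider. A 5-point gap, as large as the margin, gives 6.25/132.25 = 4.7%, and an interval about 2.5% wider. Reaching 10% would need a larger age gap or a material site effect as well.

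**Step 5. Check with attrition.** Stratified blocks of 6 or 8 were simulated with 300 randomised, 25% of outcomes missing, 4 sites (assumed) and 6,000 runs per scenario. The adjusted model used additive site and age terms.

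| Assumed R² | Mean half-width, unadjusted / adjusted | One-sided error at the margin, unadjusted / adjusted |
|---|---|---|
| 0 | 3.02 / 3.03 | 0.026 / 0.026 |
| 5% | 3.02 / 2.95 | 0.023 / 0.025 |
| 10% | 3.02 / 2.87 | 0.022 / 0.027 |

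Monte Carlo error on the error rates is about 0.002. The direction agrees with Step 3. The unadjusted test is a little less conservative than under perfect balance, because missing outcomes loosen the balance. If the strata explain nothing, adjusting costs about 0.01 points of half-width.

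**The case against.** The main objection is that the sentence names treatment as a main effect without saying that it is the only term. This is a journal article, and a covariate list may sit in an analysis plan that is not shown. That has some force: the word 'only' is an inference. But the article does name model terms when it means to. Its quality-adjusted life year model, under Health economic analysis, lists a random intercept, categorical time and baseline adjustment. For the model that decides the trial, one term is named. A decision model that can be read two ways needs the same one-line clarification.

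The second objection is about size, and it stands. Nothing in the article shows that site predicts PROMIS, and for age it says only that healing may differ. At R² of 2% the interval is 1% wider, and at zero there is no gain at all.

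Three stronger readings are tempting, and the article does not support them.
- **That the trial is underpowered.** It is not: 112 per arm follows from the unadjusted SD, so leaving the strata out forgoes power above the target rather than losing any of the 90%.
- **That the buckle-fracture analysis suffers most because it is smaller.** Its half-width, 1.96 × 7.5 × √(2/48) = 3.00, is practically that of the main analysis. The subgroup is identified by the expert panel after randomisation, so the blocks do not secure balance within it. Simulated with 12 strata (assumed), its unadjusted one-sided error stayed near nominal, at 0.024 and 0.023 for R² of 5 and 10% (Monte Carlo error about 0.0025).
- **That the secondary-outcome models share the fault.** They are described only by type of regression, which is ordinary condensation in an article.

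**Conclusion.** The mismatch between stratified randomisation and the stated primary model is real, but its consequence is conditional and modest. If site and age explain 2 to 10% of PROMIS variance, the unadjusted interval is about 1 to 5% wider than it need be, and the one-sided error is about 0.024 to 0.019 under perfect balance, or nearer 0.025 once attrition is allowed for. If they explain nothing, there is no effect.

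The error is on the safe side for a non-inferiority claim. The estimate is not biased by leaving the strata out, false claims of non-inferiority do not become more frequent, and the planned power is met. The figures rest on the article's SD of 11.5, 112 analysed per arm and an assumed R². This is an almost costless improvement in precision and calibration, not a threat to the validity of the trial.

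**What to change.** State the primary model as PROMIS at 28 days = treatment + site + age group. Use additive terms rather than one term per site-by-age cell, with a pre-set rule for small sites (pooling, or site as a random effect). Report the unadjusted estimate as a sensitivity analysis. If the unadjusted model is in fact intended, say so and make the adjusted one the sensitivity analysis. Settle this before outcome data are seen, so that the choice between two intervals cannot follow the results.

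The cost is one sentence. Both factors are recorded by the time of randomisation, and neither the sample size nor the margin changes.

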## Data collection and management

Data will be manually collected at the initial hospital visit, later manually entered into the secure, purpose-built web-based database, REDCap® (Research Electronic Data Capture, Vanderbilt University, Nashville, TN, USA), and then via automated electronic surveys directly linked to the database, emailed to participants after discharge at the designated timepoints, generally a combination of 1, 4 and 8 weeks (Figs. 1 and 2). If the electronic surveys have not been returned, parents will receive a phone call within 48 h to remind them to complete and submit them. A maximum of 5 attempts to contact parents or secondary contacts by either telephone, text message or email will be made by the research team. If there is no response after the 5th attempt, the participant will be considered lost to follow-up for that time point but will still be contacted at subsequent time points, unless the patient withdraws from the trial.

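### The primary analysis is said to include all randomised children, but a 28-day regression with no imputation makes it an available-case analysis, and the unqualified rule shuts out imputation-based sensitivity analyses

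*Protocol article*

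**What the plan says.** All references are to the protocol article.

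- **Statistical methods, analysis set:** "Primary analyses will include all randomised patients". The analysis follows intention to treat, with a secondary per-protocol analysis.
- **Statistical methods, model:** linear regression of the between-group difference at 28 days, with treatment group as a main effect. Non-inferiority is claimed if the whole 95% confidence interval lies above the margin.
- **Statistical methods, missing data:** "Missing data will not be imputed". No exception is given.
- **Sample size:** outcome data are needed on 224 children, 112 per arm. Recruitment continues until that count, and a count of buckle fractures, is reached. "Allowing for approximately 25% attrition", together with variation in buckle fracture prevalence, up to 300 children are expected to be recruited.
- **Data collection and management:** after five unanswered contact attempts, "the participant will be considered lost to follow-up for that time point but will still be contacted at subsequent time points".
- **Blinding and Functional outcome:** the trial is open-label. PROMIS is self-reported from age 8 and proxy-reported below that age.

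**The concern.** Two stated rules conflict. An analysis that includes every randomised child needs some way to handle a child with no 28-day score. A single-time-point regression without imputation has none, so the child leaves the analysis. The plan expects such children: it budgets for attrition and defines recruitment by the number who do supply the outcome.

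Available-case analysis is a legitimate choice, but it should be named as one. It estimates the all-randomised difference only if the children who did not answer would have shown the same between-arm difference as those who did. Families know the allocation and report the outcome themselves or for their child, so response could plausibly depend on arm and on recovery. The document neither shows nor rules this out. If the unobserved POCUS children did worse, the completers' comparison would favour POCUS, which is the direction of a false non-inferiority claim. The usual way to examine this is to impute the missing scores under progressively worse assumptions, and the rule as written does not allow it.

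**Working it through.** **Inputs, all from Sample size.** Margin: "non-inferiority margin defined as an absolute difference of 5 points". Design difference: "the true between-group difference was assumed to be zero". Spread: "the standard deviation of PROMIS assumed to be 11.5 points". One-sided α 0.025, power 90%, 112 per arm with outcome data, up to 300 recruited, about 25% attrition.

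**1. Reproduce the plan's figures.**
- n per arm = 2 × 11.5² × (1.960 + 1.282)² / 5² = 111.2, rounded up to 112. This matches.
- 224 / (1 − 0.25) = 298.7, so 299, against the stated 300. Attrition of 25% alone accounts for the recruitment figure.

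**2. Children outside the regression.** 300 × 0.25 = 75. Equivalently, 300 − 224 = 76, or 25.3%. Either is the number at the recruitment ceiling, not a forecast of loss.

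**3. Slack at the planned size.**
- SE = 11.5 × √(2/112) = 1.54
- 95% half-width = 1.96 × 1.537 = 3.01
- At an observed difference of 0 the lower limit is −3.01, so the slack to −5 is 5 − 3.01 = 1.99 points.

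**4. Tipping point.** Let m be the share missing in each arm, d the difference (POCUS minus x-ray) among completers, and d − δ the difference among the missing. The all-randomised difference is (1 − m)d + m(d − δ) = d − mδ. With the half-width held at the completers' value, the verdict flips when mδ exceeds the slack, that is when δ > (1.99 + d)/m.

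| d | δ at m = 10% | δ at m = 15% | δ at m = 25% |
|---|---|---|---|
| 0 | 19.9 | 13.3 | 8.0 |
| −1 | 9.9 | 6.6 | 4.0 |
| −1.9 | 0.9 | 0.6 | 0.35 |

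δ is measured beyond the completers' difference. At d = 0 and m = 25%, the gap among the missing is 7.95 points (7.95/11.5 = 0.69 SD). At d = −1 the gap among the missing is −1 − 3.95 = −4.95 in total.

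Holding the half-width is one convention. If all 300 children carried full information, SE = 11.5 × √(2/150) = 1.33, the half-width is 2.60, and the flip at d = 0 needs (5 − 2.60)/0.25 = 9.6 points.

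**5. Effect on the error rate.** Suppose the true all-randomised difference is exactly −5 and m = 25%. The completers' expected difference is then −5 + 0.25δ, and the chance of a false claim is Φ(0.25δ/1.537 − 1.96).

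| δ (assumed) | False-claim probability |
|---|---|
| 0 | 2.5% |
| 2 | 5.1% |
| 4 | 9.5% |
| 8 | 25.5% |

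These values of δ are assumptions chosen to show a range. The documents give no basis for predicting one.

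**The case against.** **The phrase about all randomised patients may only set the whole cohort against the buckle-fracture subgroup.** The next sentence but none other introduces that subgroup, and elsewhere the article openly counts children with outcome data. Intention to treat is also often used to mean analysed as allocated. This is a fair reading and it makes the conflict one of wording. It does not remove it, because the sentence reads as a definition of the analysis set that the stated method cannot deliver.

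**A reader might infer that the trial has no sensitivity check, or no way to test the effect of dropout.** The documents do not support either. The analysis plan is not shown and may contain such an analysis, so silence in the article is no finding. Checks that impute nothing also remain open, such as a repeated-measures model, inverse-probability weighting, or a comparison of responders with non-responders. What stands is narrower: the published rule is unqualified, so any imputation-based check would contradict it. The per-protocol analysis does not fill the gap, because under the same rule it too uses only observed outcomes.

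**A reader might take 75 missing children as the expected loss.** The 25% is a planning allowance stated together with variation in buckle prevalence, and 300 is a ceiling. The article describes email, text and telephone reminders and completion by phone. Recruitment also continues until 112 per arm have data, so precision is protected and only bias is at issue.

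**A reader might conclude that the primary model must become a repeated-measures model.** The article implies that PROMIS is completed more than once, but the schedule is in a figure not shown. A 28-day regression matches the stated 28-day outcome. A repeated-measures model would also rest on data being missing at random, so it would not settle informative dropout.

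**The gap needed at an observed difference of 0 is large.** It is 7.95/5 = 1.6 times the margin. This is correct and limits the point.

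**Conclusion.** The point holds in a limited form. The stated analysis set, the stated model and the missing-data rule cannot all be met once any child lacks a 28-day score, and the plan allows for up to about 75 such children. The primary analysis is in effect an available-case analysis, and the blanket rule excludes imputation-based examination of it.

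The consequence depends on two things the documents do not settle: how many children are missing, and whether the missing children differ by arm. If they do not, there is no bias. With 25% missing in each arm, an observed difference of 0 is moderately robust (about 8 points to tip), −1 is less so (about 4 points beyond the observed difference), and a result close to the margin is fragile. With 10% missing, the tipping values are two and a half times as large. This should be corrected, but it does not invalidate the design.

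**What to change.** 1. Describe the primary set as all randomised children with 28-day PROMIS data, analysed in the arm to which they were allocated.
2. Limit the no-imputation rule to the primary analysis.
3. Pre-specify a delta-adjusted (tipping-point) sensitivity analysis that worsens the missing POCUS scores step by step until the lower confidence limit crosses the 5-point margin, and report the delta at which this happens.
4. Optional: if PROMIS is also collected at other visits, add a repeated-measures model using those scores as a further sensitivity analysis. It need not replace the primary regression.

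The 224 and 300 stay as they are. The cost is a change of wording and modest programming. If the analysis plan already contains item 3, only the article's wording needs to be brought into line with it.
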